### Other measures

i)Co-interventions: At 24 weeks, participants will be asked to fill in a custom-devised table indicating their frequency of use of a range of other hip treatments (over the past 24 weeks).ii)Website visits: Participants will be asked “How many times did you visit the website over the past 2 months?” with response options “never”, “1–5 times”, “6–10 times” and “ > 10 times” at 8, 16 and 24 weeks;iii)Leg strengthening exercise (control group only): At 24 weeks, participants will be asked “Over the past 24 weeks, did you perform leg strengthening exercise one or more times a week for at least 8 weeks?” with response options yes/no.

The intervention group will be asked additional questions at 24 weeks, unless otherwise stated, including:i)Downloaded the three exercise programs: response options of yes/no for each;ii)Number of days strengthening exercises performed: Participants will be asked “In the past two weeks, on how many days did you perform the strengthening exercises from the “My Hip Exercise” program (0–14)” at 8, 16 and 24 weeks. Responses will be summed over the three time points and reported as the average number of days per week;iii)Exercise Adherence Rating Scale (EARS) Section B [53] scored from 6 items with scores ranging from 0–24, higher scores indicating better adherence;iv)Downloaded My Exercise Messages app: response options of yes/no;v)Frequency of entering exercise information into app: Scored on a 5-point Likert scale for “How often did you enter your number of exercise days into the app as requested” with response options of never/ rarely/sometimes/often/always;vi)Use of the app: At 8, 16 and 24 weeks, participants will be asked “On how many days in the past 14 days did you use the “My Exercise Messages” app (including reading any notifications, entering data and/or opening the app)” with response options “never”, “1–5 times”, “6–10 times” and “ > 10 times” at 8, 16 and 24 weeks;vii)Usefulness of the website: Scored on an 11-point NRS from 0 = “not at all useful” to 10 = “extremely useful”;viii)Usefulness of the app: Scored on an 11-point NRS from 0 = “not at all useful” to 10 = “extremely useful”;ix)Exercise equipment use: Participants will be asked “Did you use exercise equipment (such as weights or elastic bands) to add resistance to your leg for your strengthening exercises?” with response options of yes/no;x)Registered for two recommended external website programs (“Taking Control of Your Hip and Knee Osteoarthritis” and ‘PainTrainer”): response options of yes/no for each.

### Descriptive measures

Baseline self-reported descriptive measures include age, sex, gender, height, weight, body mass index (calculated from height and weight), ethnicity, geographical location determined based on residential postcode, education level, employment status, comorbidities assessed using the Self-Administered Comorbidity Questionnaire [40], symptoms in other joints, hip symptom duration, and pain medication usage.

### Adverse events

Related adverse events will be defined as “any problem experienced in the study hip or elsewhere in the body deemed to be a result of participating in the trial and at least one of i) caused negative/adverse symptoms/effects for two days or more, and/or ii) resulted in the participant seeking treatment or taking medication”. Adverse events will be ascertained by survey questions to participants at 24 weeks.

A serious adverse event is defined as any untoward medical occurrence that; i) results in death; ii) is life-threatening; iii) requires hospitalisation or prolongation of existing inpatient hospitalisation; iv) results in persistent or significant disability or incapacity; v) is a congenital anomaly or birth defect, or; vi) any other important medical condition which, although not included in the above, may require medical or surgical intervention to prevent one of the outcomes listed. Due to the low-risk nature of the interventions in this trial, related serious adverse events are extremely unlikely. Participants will be advised to report any serious adverse events to the Trial Coordinator as soon as they can by telephone or email, which will be documented and reported to the Sponsor (University of Melbourne) within 24 h of the research staff becoming aware of the event. Any adverse events will be reported to the internal Trial Monitoring Committee who will be responsible for deciding on a case-by-case basis what action, if any, is required and whether the adverse events are likely to be related to the intervention.

We will report the number and proportion of participants who: withdraw from the study due to a related adverse event; experience one or more serious related adverse events and their types; and experience one or more non-serious related adverse events and their types.

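### Every planned harms summary is limited to events judged related to the trial, which leaves it open to differential attribution, and no all-cause count is planned as a check

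*Protocol article*

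**What the plan says.** All of the rules are in the protocol article, Methods, Adverse events.

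- **Definition.** Only related adverse events are defined. The problem must be "deemed to be a result of participating in the trial" and must also have caused symptoms for at least two days or led to treatment or medication.
- **Collection.** "Adverse events will be ascertained by survey questions to participants at 24 weeks". No restriction to one arm is stated.
- **Serious events.** These are defined without reference to cause. "Participants will be advised to report any serious adverse events to the Trial Coordinator as soon as they can by telephone or email", and they then go to the sponsor within 24 hours.
- **Adjudication.** An internal Trial Monitoring Committee receives any adverse events and decides, case by case, "whether the adverse events are likely to be related to the intervention".
- **Reporting.** The article promises the number and proportion of participants who "withdraw from the study due to a related adverse event", who "experience one or more serious related adverse events and their types", and who "experience one or more non-serious related adverse events and their types". No count irrespective of cause is listed.

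The Interventions section describes what each arm receives. The exercise arm has a 24-week home strengthening program, three times a week, at a perceived exertion of hard to very hard. The control arm has the educational content and general guidance on exercise and activity, without a strengthening program.

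**The concern.** Relatedness is a judgement made after randomisation, with the participant's experience of the allocated program in view. The same hip flare may be more readily put down to the trial in someone doing demanding leg exercises than in someone following general advice. When every reported quantity passes through that judgement, a difference between arms can reflect a difference in events, a difference in attribution, or both, and the reader cannot tell which.

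The error can go either way. Readier attribution in the exercise arm would overstate its harms. Real exercise harms wrongly judged unrelated would disappear from the report. Serious events show the gap most clearly: a hospitalisation judged unrelated would be collected and sent to the sponsor, yet would fall outside all three reported summaries. The Discussion section says the trial's measures will inform on safety, and a list filtered by attribution alone supports that only weakly.

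**Working it through.** **The plan's own figures.** The article gives no expected adverse event rate and no attribution rate, so there is no harms figure to reproduce. The sample size does not enter the argument.

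**Step 1: what is collected against what is reported.**

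| | Collected | Listed for reporting |
|---|---|---|
| Serious events | Any cause | Related only |
| Non-serious events | By survey at 24 weeks, wording not shown | Related only |
| Withdrawals | Not described in this section | Due to a related event only |

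**Step 2: how attribution enters the reported proportion.** Let p be the true proportion with at least one qualifying event, assumed the same in both arms. Let a_I and a_C be the probabilities that a participant with a qualifying event has it judged related, in the exercise and control arms.

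- Reported proportions: p × a_I and p × a_C
- Reported risk ratio: (p × a_I) / (p × a_C) = a_I / a_C, whatever the value of p
- Reported risk difference: p × (a_I − a_C)

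**Step 3: illustration.** All values are assumptions, with p = 0.20.

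| a_I | a_C | Exercise | Control | Risk ratio | Difference |
|---|---|---|---|---|---|
| 0.50 | 0.50 | 0.20 × 0.50 = 10% | 0.20 × 0.50 = 10% | 1 | 0 points |
| 0.50 | 0.25 | 10% | 0.20 × 0.25 = 5% | 2 | 5 points |
| 0.50 | 0.10 | 10% | 0.20 × 0.10 = 2% | 5 | 8 points |
| 0.50 | 0 | 10% | 0% | undefined | 10 points |

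For attribution of 0.50 against 0.25, varying p from 0.10 to 0.40 moves the spurious difference from 0.10 × 0.25 = 2.5 points to 0.40 × 0.25 = 10 points. The first row matters as much as the others: equal attribution produces no distortion.

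**Step 4: the two referents.** The definition ties relatedness to taking part in the trial, a test that applies to both arms. The committee's test is relatedness to the intervention. The Interventions section covers both arms, but Table 1 uses the term intervention group for the exercise arm only. If the committee's wording were read in that narrower sense, no control event could qualify, which is the last row of the table. The article does not say which test determines the reported count.

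**The case against.** A reader might infer that the harms comparison is biased by construction because controls have nothing to blame. The documents do not support that, for these reasons:

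- **Controls have something to attribute events to.** They receive general exercise and activity guidance and most of the educational content, and they may act on it. The trial asks them at 24 weeks whether they did leg strengthening. Relatedness to trial participation can apply to them.
- **Bias needs unequal attribution.** This is plausible but not established. Participants are under limited disclosure and are not told which resource is under test, although they do know whether they followed a strengthening program.
- **Who attributes is not stated.** The definition is in the passive, and the only named decision-maker is the committee. The survey might ask about all problems and leave relatedness to adjudication. Its wording is not shown.
- **Committee masking is not described.** In a condensed article this may simply be left to the full protocol, so the silence is not itself a fault.
- **No formal harms test is named.** The article promises numbers and proportions, and Table 1 lists adverse events under other measures.
- **Hip worsening is also captured without attribution**, through walking pain, the HOOS pain subscale, global change and pain medication use. That does not cover events elsewhere in the body or serious events.

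These points remove the claim of certain bias. They do not answer the reporting rule, which the article states expressly: all three summaries are restricted to related events. Side-by-side proportions in a two-arm trial will be read as a comparison whether or not a test is attached.

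**Conclusion.** The point holds as a conditional risk created by a stated reporting rule. The planned summaries depend wholly on relatedness judgements that may differ between arms, and no all-cause summary is planned against which to check them. With equal true rates the reported risk ratio is a_I / a_C. The documents give no basis for its value, so the percentages above show the mechanism and do not estimate this trial's bias. The likelier direction is to overstate harm in the exercise arm, but the reverse is possible. The primary and secondary outcome analyses are unaffected. The change is worth making because it is cheap and because an all-cause comparison between randomised arms needs no attribution.

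**What to change.** 1. Report by arm, first, the number and proportion of participants with any serious adverse event, and with any adverse event meeting the existing severity test, regardless of relatedness. Then give the related subset as now planned.
2. If the 24-week survey asks only about problems the participant attributes to the trial, drop that condition from the question, in both arms alike.
3. Have relatedness judged from accounts with arm details removed where feasible. Some accounts will reveal the arm, so this will be incomplete.
4. Reconcile the two referents, trial participation and the intervention, and state which judgement determines the reported count.

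The cost is two extra table rows, possibly one reworded survey item, and more unrelated complaints listed. The all-cause serious-event row needs no new data. It and the masked judgement of relatedness remain possible even if the survey can no longer be altered.

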### Outcome measures

Table 1 lists all descriptive data, primary and secondary outcomes, and other measures. Participant-reported outcomes will be collected online via REDCap data capture platform and, unless otherwise indicated, collection is at baseline and 24 weeks after randomisation. Some process measures are also collected at 8 and 16 weeks.

**Table 1 Tab1:** Schedule of enrolment, intervention and assessments

	**Enrolment**	**Allocation**	**Secondary**		**Primary**
**Timepoint**		***0w***	***8w, 16w***		***24w***

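### Non-serious adverse events are solicited only once, at week 24 when the programme ends, although both arms already answer surveys at weeks 8 and 16

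*Protocol article*

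**What the plan says.** The Adverse events section of the protocol article fixes how events are collected: "Adverse events will be ascertained by survey questions to participants at 24 weeks". Table 1 agrees, with a mark in the 24-week column only. A related event counts if it lasted two days or more, or led the participant to seek treatment or take medication.

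Serious events have their own route: "Participants will be advised to report any serious adverse events to the Trial Coordinator as soon as they can by telephone or email". Such an event is then "reported to the Sponsor (University of Melbourne) within 24 h of the research staff becoming aware of the event".

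Any adverse event goes to an internal Trial Monitoring Committee, whose task is given as "deciding on a case-by-case basis what action, if any, is required and whether the adverse events are likely to be related to the intervention". Among the results promised is the number and proportion of participants who "withdraw from the study due to a related adverse event".

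Under Outcome measures the article says: "Some process measures are also collected at 8 and 16 weeks". One of these measures, website visits, is asked of both arms "at 8, 16 and 24 weeks" (Other measures).

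**The concern.** The programme runs for 24 weeks, unsupervised, three times a week, at an effort rated hard to very hard for most exercises. The only question that solicits non-serious events comes when that exposure is over. Three things follow.

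- **Recall.** One question has to cover the whole period. An event of two days in the first weeks is easily forgotten or misdated by week 24.
- **Loss.** People who do not reach the 24-week survey are not, on any route described, asked about non-serious events.
- **Oversight.** The committee is asked to decide on action, but for a non-serious event first reported at week 24 the affected participant has no programme left to act on.

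The Discussion says the trial will provide information on the programme's safety. What is at stake is how complete that account is. The primary outcomes and the sample size are not affected.

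**Working it through.** **Inputs**

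- Programme length 24 weeks, three sessions a week (Abstract; My hip strength).
- 91 participants per arm, 182 in total, 15% loss to follow-up (Sample size).
- Solicited adverse-event time points: week 24 only (Adverse events; Table 1).
- Survey contacts in both arms: weeks 8, 16 and 24 (Table 1; Other measures).
- Recruitment from March 2023 to an anticipated September 2024 (Timelines).

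**The plan's own figure.** The 15% is an allowance inside the sample size, so I checked how it enters. Function drives the number. The baseline-adjusted SD is 13 × √(1 − 0.40²) = 11.9. For a difference of 6, two-sided alpha 0.025 and 80% power, an exact t calculation gives 77 per arm. Then 77 / 0.85 = 90.6, rounded up to 91 per arm and 182 in total. The stated figure is reproduced, and 15% is a straightforward expected proportion lost by week 24.

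**People not reached by the single survey**

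- Lost: 0.15 × 182 = 27.3, about 27 (0.15 × 91 = 13.65, about 14 per arm).
- Expected to answer: 0.85 × 182 = 154.7, about 155 (about 77 per arm).

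**Share of participants with a non-serious event who go unseen.** Let m be the risk in people lost relative to completers. If nobody lost is asked,

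unseen share = 0.15m / (0.85 + 0.15m).

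| m | Calculation | Unseen share |
|---|---|---|
| 1 | 0.15 / 1.00 | 15% |
| 1.5 | 0.225 / 1.075 | 21% |
| 2 | 0.30 / 1.15 | 26% |
| 3 | 0.45 / 1.30 | 35% |

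The documents give no value for m; these are assumptions that show the range. The shares are upper figures to the extent that events are recorded when someone withdraws.

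**Recall and exposure.** One question at week 24 spans up to 24 weeks, or 24 × 3 = 72 prescribed sessions. With questions at weeks 8, 16 and 24 each window is about 8 weeks, or 8 × 3 = 24 sessions.

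**Harms beside engagement in the same plan**

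| Measure | Times asked | Recall window |
|---|---|---|
| Exercise days (intervention arm) | 3 | 2 weeks |
| App use (intervention arm) | 3 | 14 days |
| Website visits (both arms) | 3 | 2 months |
| Non-serious adverse events (both arms) | 1 | up to 24 weeks |

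Engagement is thus measured three times with short recall, and harms once with the longest.

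**Timing for the committee.** A participant randomised in March 2023 reaches week 24 in August or September 2023, about a year before recruitment is due to end.

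**The case against.** The strongest reply is that the plan has more safety cover than the single survey suggests. Three stronger readings might be inferred, and the document supports none of them.

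*That the committee cannot act in time on any adverse event.* Serious events can be reported throughout, and the sponsor hears within 24 hours of staff becoming aware. The route relies on the participant coming forward, but it is continuous. Because recruitment is staggered, early 24-week reports of non-serious events can also inform action for later participants, and judging relatedness does not require the programme to be running. What stands is narrower: for a non-serious event, nothing can be done for that same participant during the programme.

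*That everyone who drops out is missed.* The promise to report withdrawals due to a related event implies some capture at withdrawal, and an article may leave the mechanics to the full protocol. What stands is that no solicitation of non-serious events is described for people lost before week 24. Those lost without any contact would remain unseen, and some would skip added surveys too.

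*That events are under-counted more in the exercise arm.* This is possible, but the document gives no differential loss or event rates and no timing of drop-out. Event-driven withdrawal is also the one kind of loss the plan says it will count.

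It is fair to add that the authors regard the interventions as low risk, that participants with a recent fall, housebound status or flagged health conditions need medical clearance, that the definition excludes the most trivial events, and that adverse events are neither a primary nor a secondary outcome. These points lower the stakes. They do not explain why surveys already going to both arms leave the question out.

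**Conclusion.** The point holds for non-serious adverse events. As written, they are solicited once, at the end of exposure, with recall of up to 24 weeks and no described solicitation from people lost earlier. At the planned 15% loss that is about 27 of 182 participants. Between 15% and 35% of participants with an event would go unseen if those lost carry one to three times the risk of completers and none of them is asked. The 15% is a planning allowance rather than an observed non-response rate, and the risk ratios are assumptions. The direction of any bias between arms cannot be settled from the document. This is a cheap improvement to the harms data that should be made; it does not threaten the trial's primary conclusions.

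**What to change.** 1. Add the same adverse-event item to the existing 8- and 16-week online surveys in both arms, covering the past 8 weeks, and ask it at any withdrawal contact. Identical wording in both arms keeps the comparison symmetrical.
2. Make the 24-week item cover the time since the last survey answered, so that a missed survey leaves no gap.
3. Mark Table 1 at weeks 8 and 16 for adverse events, and forward reports to the committee as they arrive.
4. Report events by arm and by ascertainment schedule. Define the schedule by which surveys carried the item when the participant was due them, not by which were answered, so that the comparison of arms within a schedule stays randomised.

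**Cost.** A minor ethics amendment and slightly longer surveys. Recruitment began in March 2023, so participants already past week 8 or week 16 will have fewer questions, or only the single 24-week recall. Repeated asking tends to bring out more events, so a pooled count would mix two methods of ascertainment; that is why item 4 is needed. Sample size and primary analysis are unchanged.

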### Sample size 

We based the sample size on detecting a difference in change between-groups that meets or exceeds a specified minimal clinically important difference (MCID) for the two primary outcomes of hip pain on walking and WOMAC physical function. The MCIDs we used were 1.8 units for NRS hip pain [54] and 6 units for WOMAC physical function [55]. To achieve 80% power and a two-sided 5% significance level split equally across the two primary outcomes, assuming equal between-participant standard deviations of 2.5 for pain and 13 for function for both groups and a correlation between pre- and post-measurements of 0.25 for pain and 0.40 for function [56], and accounting for 15% loss to follow up, we required 91 participants per arm, for a total of 182 participants. We will consider the intervention to be effective if at least one of the two primary outcomes shows a significant between-group difference.

### Data analysis plan

An a priori statistical analysis plan will be published on the Centre for Health, Exercise and Sports Medicine’s website. A statistician blinded to group details will perform analyses comparing the two groups. An intention-to-treat analysis will be conducted using data available from all randomised study participants. Multiple imputation will be conducted, and the method reported if the amount of missing data for either primary outcome is greater than 5%. The primary analysis will then use multiply imputed datasets, with a sensitivity analysis using complete case datasets.

A summary of participant demographics and baseline characteristics will be presented. Linear regression models, adjusted for baseline levels of the outcome, will be used to compare mean differences in change (baseline minus follow up) for continuous variables. Standard diagnostic plots will be used to assess model assumptions. Each primary outcome will also be dichotomised into those who do and do not achieve the MCID in improvement in hip pain on walking and function to aid clinical interpretation of results. For these and other binary outcomes, groups will be compared using risk differences and risk ratios, calculated from logistic regression models and adjusted for the outcomes at baseline where available.

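### The sensitivity analysis named for missing primary outcomes, complete case, rests on essentially the same missing-at-random condition as the imputed primary analysis, so agreement between them says nothing about informative loss

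*Protocol article*

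**What the plan says.** The protocol article, Data analysis plan, sets the trigger: "Multiple imputation will be conducted, and the method reported if the amount of missing data for either primary outcome is greater than 5" per cent. It then fixes the pair of analyses: "The primary analysis will then use multiply imputed datasets, with a sensitivity analysis using complete case datasets". No other analysis for missing primary outcomes is named in the article. The same section announces a separate statistical analysis plan, which is not available here.

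The analysis model is in the same section: "Linear regression models, adjusted for baseline levels of the outcome, will be used to compare mean differences in change". Change is defined there as baseline minus follow-up, so a positive group difference favours the intervention.

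On timing, Outcome measures says that, unless otherwise indicated, "collection is at baseline and 24 weeks after randomisation". Table 1 shows both primary outcomes at those two points only. At 8 and 16 weeks only process measures are collected: website visits in both arms, and exercise days and app use in the intervention arm.

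On expected loss, the Sample size section reads: "and accounting for 15% loss to follow up, we required 91 participants per arm, for a total of 182 participants".

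**The concern.** A sensitivity analysis is useful when it relaxes an assumption that the primary analysis cannot check. Here the uncheckable assumption is that participants without 24-week data fared as the model predicts from those who responded.

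There is one follow-up measurement of each primary outcome, and baseline is completed before allocation is revealed. Suppose imputation uses arm and the baseline outcome. It then draws the missing values from the regression fitted to the responders, and refitting that regression to the completed data returns the complete-case estimate plus Monte Carlo noise. Both analyses make the same assumption, so their agreement could be reported as robustness although the assumption was never varied.

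What is at stake is a result near the boundary. The Sample size section counts the intervention as effective if at least one of the two primary outcomes is significant, so one borderline result can settle the trial's conclusion. Outcome-related loss is not far-fetched: the Adverse events section plans to report withdrawals due to related adverse events, which may include problems in the study hip.

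**Working it through.** **Inputs (Sample size section).** SD 2.5 (pain) and 13 (function); pre-post correlation 0.25 and 0.40; MCIDs 1.8 NRS and 6 WOMAC; 80% power; two-sided 5% split equally, so 0.025 per outcome; 15% loss; 91 per arm.

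**1. Reproduce the plan's sample size.**
- Residual SD after baseline adjustment = SD × √(1 − r²). Function: 13 × √(1 − 0.16) = 11.91. Pain: 2.5 × √(1 − 0.0625) = 2.42.
- Noncentral-t calculation at alpha 0.025 and 80% power: function needs 77 per arm, and 77/0.85 = 90.6, so 91. This matches the plan. Pain needs 36, inflated to 43, so function drives the size.
- Expected completers: 91 × 0.85 = 77.35, about 77 per arm.

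**2. Do the two analyses differ under informative loss?** Simulation with 91 per arm, 1,500 trials per scenario, 20 imputations from arm and baseline outcome. Assumptions not in the documents: the imputation model, and a shift d by which the missing participants are worse than missing at random predicts. Loss is 15% per arm with the shift in the intervention arm only, except in the rows marked 20%/10% (intervention/control), where both arms have the same shift.

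| Outcome | d | Full-data effect | Complete case | MI |
|---|---|---|---|---|
| Pain | 0 | 1.81 | 1.80 | 1.80 |
| Pain | 1 | 1.66 | 1.81 | 1.81 |
| Pain | 2 | 1.49 | 1.78 | 1.78 |
| Pain, 20%/10% | 2 | 1.61 | 1.81 | 1.81 |
| Function | 0 | 5.95 | 5.98 | 5.98 |
| Function | 6 | 5.06 | 6.02 | 6.02 |
| Function | 10 | 4.46 | 5.93 | 5.93 |
| Function, 20%/10% | 10 | 5.06 | 6.06 | 6.06 |

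The average complete-case and MI estimates agree within 0.01 in every row. Within a single trial they differ on average by about 0.03 NRS points or 0.13 WOMAC units, against sampling SDs of about 0.39 and 1.9.

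**3. Size of the bias.** To first order, bias = (fraction missing × shift) in the intervention arm minus the same product in the control arm.
- 15% missing, shift in one arm: 0.15 × 2 = 0.30 NRS; 0.15 × 6 = 0.90 and 0.15 × 10 = 1.50 WOMAC. The simulated gaps are 0.30, 0.97 and 1.47.
- 20%/10% with shift 10 in both arms: 0.20 × 10 − 0.10 × 10 = 1.0. The simulated gap is 1.01.
- Equal loss with equal shifts cancels.

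**4. When would this change a conclusion?** Take 77 per arm and the two-sided 0.025 critical value t ≈ 2.264, and treat the standard error as unchanged by the shift.
- Standard error: function 11.91 × √(2/77) = 1.920; pain 2.42 × √(2/77) = 0.390.
- Critical difference: 2.264 × 1.920 = 4.35 WOMAC; 2.264 × 0.390 = 0.88 NRS.
- Tipping shift = (observed effect − critical difference)/0.15, from unrounded critical differences (4.347 and 0.883):

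| Observed effect | Tipping shift |
|---|---|
| Function 5.0 | 0.653/0.15 ≈ 4.35 |
| Function 6 (design) | 1.653/0.15 ≈ 11.0 |
| Pain 1.0 | 0.117/0.15 ≈ 0.8 |
| Pain 1.8 (design) | 0.917/0.15 ≈ 6.1 |

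The effects of 5.0 and 1.0 are chosen to lie just above significance. Their tipping shifts are below the MCIDs of 6 and 1.8; those at the design effects are well above them.

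**The case against.** Multiple imputation with a complete-case check is conventional and not self-contradictory, and a separate analysis plan is announced that may hold further analyses. A reader might infer that complete case is the only check the trial will make. The article does not support that: it is the only one named there, and the unseen plan may add others. What stands is that the article itself chooses a sensitivity analysis, and the chosen one does not vary the assumption in question.

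A reader might also infer that the two analyses must agree, or that the comparison can reveal no bias at all. Neither follows, because the article does not specify the imputation model. It could draw on other baseline variables and on the 8- and 16-week process measures. In a simulation that assumes intervention-arm loss depends on an interim auxiliary seen for everyone and correlated 0.3 or 0.5 with the outcome residual, complete case was biased by 0.7 or 1.2 WOMAC units. Imputation with the auxiliary was biased by about 0.02, so the gap was informative. This objection stands for bias that the auxiliaries explain. It does not reach loss that depends on the unseen outcome itself. The practical scope is also modest, since website visits are the only 8- and 16-week measure taken in both arms. Missingness may also differ between the two primary outcomes, which could open a further small gap.

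Finally, a reader might infer that informative loss would favour the intervention. The documents give no direction: dissatisfied controls or recovered participants may equally stop responding.

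**Conclusion.** The point holds in this form: under the rule stated in the protocol, agreement between the imputed and complete-case analyses is no evidence against bias from data missing not at random. It applies only if more than 5% of either primary outcome is missing; the 15% is a planning allowance, not a forecast of informative loss.

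The near-coincidence of the two analyses assumes imputation from arm and baseline, or from auxiliaries that add little. With 15% of one arm missing, the undetected bias is about 0.15 times the unseen shift: 0.3 NRS points for a shift of 2, and 0.9 to 1.5 WOMAC units for shifts of 6 to 10. These shifts are illustrative.

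The consequence is confined to results near the boundary. Were the trial to observe its design effects, only shifts of about 11 WOMAC units or 6 NRS points would overturn significance. The plan should be changed, but nothing here shows that the trial's result will be biased.

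**What to change.** Keep multiple imputation as the primary analysis; complete case may stay as a secondary display. Name as the sensitivity analysis, for each primary outcome, a delta-adjusted (pattern-mixture) imputation:

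- Shift the imputed values in the intervention arm, in the control arm, and in both.
- Use a range that includes the MCIDs (1.8 NRS, 6 WOMAC) and extends until the conclusion changes or the shift is implausible. A grid that stops at the MCIDs would not reach the tipping point at the design effects.
- Report the tipping point at the 0.025 level, with the number missing in each arm.

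The imputation model should also be stated in advance, including whether it uses the 8- and 16-week process measures, so that a gap between the imputed and complete-case results can be interpreted.

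The cost is analysis-plan wording, a few hours of programming on imputations already produced, and one more result to report. No new data are needed.
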